### Interim analyses {21b}

There will be no planned interim effectiveness analyses. However, an internal pilot phase has been built into the trial to allow a feasibility assessment which will examine recruitment, retention and adherence. Stop–go criteria 9 months after the first participant has been randomised will be used to determine the progression of the trial. Recruitment will be measured against the overall recruitment target. Retention will be determined by provision of primary outcome data. Adherence level will be measured using simple categories asking how much of the trial medication the participant used/took (high > 75% used/taken, more than half (50–75% used/taken), less than half (1–49% used/taken), from both treatment arms.

The SWAT will also undergo its own interim analysis which will be detailed in the SAP for the SWAT.

### Methods for additional analyses (e.g. sub-group analyses) {20b}

The trial is powered to detect overall differences between groups rather than interactions; therefore, any sub-group analyses will be regarded as exploratory. Planned sub-group analyses will be pre-specified in the SAP.

### Methods in analysis to handle protocol non-adherence and any statistical methods to handle missing data {20c}

Several strategies to investigate the effect of missing primary outcome data will be undertaken as sensitivity analyses, including the use of multiple imputation with chained equations and minimisation variables as covariates. Where the proportion of missing primary outcome data is greater than 20%, the primary analysis will use multiple imputation. More information on methods will be included within the SAP.

### Plans to give access to the full protocol, participant-level data and statistical code {31c}

De-identified participant data will be made available, upon request, in accordance with the NCTU standard operating procedures following the publication of the trial results.

## Oversight and monitoring

### Composition of the coordinating centre and trial steering committee {5d}

Initially, on-site monitoring of the BV eligibility and baseline STI sample results for recruited participants will take place at least annually at the lead site (LSH) but this may be increased/reduced as deemed necessary. Other than this, on-site monitoring will not be conducted routinely throughout the trial. Central monitoring of all trial data (across recruiting centres and participant-reported data) will be undertaken and used to assess whether sites have met any of the monitoring triggers detailed in the trial monitoring plan. The TMG will review ongoing trial data monthly and discuss the requirement for site visits if clinics meet monitoring triggers.

### Composition of the data monitoring committee, its role and reporting structure {21a}

An independent Data Monitoring Committee (DMC) will review unblinded trial data, including safety data, on a minimum annual basis. The DMC will operate in accordance with the trial-specific charter. Independent oversight will be provided by the Trial Steering Committee (TSC) who will meet at the same frequency as the DMC. Additional meetings may be called at the request of the DMC or TSC chair.

### Adverse event reporting and harms {22}

All medications used in the trial are UK-licensed drugs being administered within their licensed indications with well-characterised safety profiles. To provide secondary outcome data about the adverse events associated with the use of dequalinium chloride or any of the usual care antibiotics, only specified adverse reactions experienced during treatment will be collected on the week 4 follow-up questionnaire.

Serious adverse events (SAEs) are not anticipated in this trial; however, we will collect details of SAEs experienced via the week 4 follow-up questionnaire. Any participant who indicates they have been to the hospital in relation to their BV or BV treatment will be contacted to assess the event against the SAE reporting criteria.

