## Introduction

### Background and rationale {6a}

#### Background

Bacterial vaginosis (BV) is the most common cause of vaginal discharge in women of reproductive age. In 2019, 85,459 women were diagnosed with BV in English genitourinary medicine (GUM) clinics [1] (REF https://view.officeapps.live.com/op/view.aspx?src=https%3A%2F%2Fassets.publishing.service.gov.uk%2Fgovernment%2Fuploads%2Fsystem%2Fuploads%2Fattachment_data%2Ffile%2F1056731%2F2020_Table_4_All_STI_diagnoses_and_services_by_gender_and_sexual_risk_updated.ods&wdOrigin=BROWSELINK) and 15% of pregnant women attending an antenatal clinic have been found to have BV [2]. It is estimated that up to a third of women will get it at some time in their lives.

BV produces an offensive vaginal odour and is associated with serious sequelae [3]. It increases the acquisition of sexually transmitted infections (STIs) [4] and HIV [5] and the transmission of HIV [6]. It is associated with miscarriage, preterm birth [7] and pelvic inflammatory disease which causes infertility. [8]

The most frequently used treatment for BV in the UK is 7-day oral metronidazole. [3] This has microbiological resolution rates of 61–94% 1 month after treatment. [9] Recurrences are common, occurring in 23%, 43% and 52% of women at 1, 3 and 6 months post-treatment with metronidazole [10]. There are other antibiotic treatment regimens recommended in national guidelines using intravaginal metronidazole, intravaginal or oral clindamycin or oral tinidazole but the failure rates are similar [11]. Recurrent BV has a severe impact on quality of life [12] and vulvovaginal candidiasis often occurs following antibiotic treatment for BV. [13]

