### Intervention description {11a}

Women allocated to the dequalinium chloride arm (intervention) will be asked to follow the UK-licensed treatment course of one 10-mg vaginal tablet for 6 nights.

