**Interventions**						
**j** – Dequalinium chloride (intervention group)			**X** (days 1–6)			
**k** – Usual care antibiotics (control group)			**X** (duration of treatment in accordance with usual care)			

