## Assignment of interventions: blinding

### Who will be blinded {17a}

Blinding of the participant and site research team is not possible due to the nature of the intervention; several different usual care antibiotics with different routes, formulations and duration will be used in the control arm.

Central laboratory staff performing BV microscopy and STI testing will be blinded to the participant’s treatment allocation. The chief investigator, deputy chief investigator and trial management team will be blinded to the treatment allocation of participants recruited in the trial. Trial and senior trial statisticians will be blinded to participants’ treatment allocation, including other data with the potential to lead to unblinding, until after the statistical analysis plan (SAP) is finalised and approved and the trial database (including randomisation system) is locked. Any data summaries and analyses which require knowledge of the treatment allocation, e.g. within the closed report for the Data Monitoring Committee (DMC), will be conducted by a statistician who is independent of the trial. Such summaries and analyses will be held in an area which is accessible only to the statistician(s) who are independent of the trial.

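### Specified side effects are counted only if they occur during the treatment course, so candidiasis starting after the course is left out of the harms outcome

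*Protocol article*

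**What the plan says.** The harms section ({22}) gives the purpose of the side-effect data as follows: "To provide secondary outcome data about the adverse events associated with the use of dequalinium chloride or any of the usual care antibiotics". It then sets the collection rule: "only specified adverse reactions experienced during treatment will be collected on the week 4 follow-up questionnaire". Serious adverse events are sought through the same questionnaire, and no on-treatment limit is stated for them.

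The Background says of the control class that "vulvovaginal candidiasis often occurs following antibiotic treatment for BV". It gives neither a rate nor a time of onset.

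On course length, the intervention is "one 10-mg vaginal tablet for 6 nights" ({11a}). For control, the Background says "The most frequently used treatment for BV in the UK is 7-day oral metronidazole", and Table 1 gives only "duration of treatment in accordance with usual care". The blinding section ({17a}) adds that "several different usual care antibiotics with different routes, formulations and duration will be used in the control arm".

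The statistical methods section ({20a}) plans a descriptive summary of side effects by the treatment actually received. It names no common time window. Data management ({19}) places the questionnaires at 4 and 12 weeks after treatment start.

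**The concern.** The one treatment-related harm that the Background names for antibiotics is described as following treatment, yet the collection rule stops when treatment stops. This is a rule about which data are gathered. Whatever the statistical analysis plan says, it cannot recover events that the questionnaire did not ask about.

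At stake is the descriptive harms comparison. In a non-inferiority trial, readers who accept similar effectiveness will look next at tolerability. If candidiasis after antibiotics is a real disadvantage of usual care, the rule could hide part of it. It could equally hide a delayed reaction to dequalinium. The direction is not known in advance.

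**Working it through.** The plan states no figure for side effects, so none can be reproduced. The check sets the stated windows side by side.

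**Inputs**
- Questionnaire at 4 weeks (28 days) after treatment start: {19}.
- Dequalinium course, 6 days: {11a} and Table 1.
- Most frequent control regimen, 7 days: Background. No other control duration is given.
- Counting rule, during treatment only: {22}.
- Candidiasis rate and onset time: not given.

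**Share of the four weeks that is covered**
- Dequalinium: 6/28 = 21%, leaving 28 − 6 = 22 days uncounted.
- 7-day metronidazole: 7/28 = 25%, leaving 28 − 7 = 21 days uncounted.
- Difference between the two windows: 1 day (7/6 = 1.17).

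**Share of events that is missed**

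The figures above are shares of time. Without onset times, the share of events missed lies anywhere between 0% (every onset during the course) and 100% (every onset after it).

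As an illustration only, assume a constant daily hazard and a 28-day risk r. The risk recorded over d days is 1 − (1 − r)^(d/28).

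| Assumed 28-day risk | Recorded over 6 days | Recorded over 7 days |
|---|---|---|
| 5% | 1.1% | 1.3% |
| 10% | 2.2% | 2.6% |
| 20% | 4.7% | 5.4% |

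At r = 10%, for example, 1 − 0.9^(6/28) = 2.2%. The missed share in this table is about 73% to 78%, but that follows almost entirely from the assumed flat hazard. It is not an estimate for this trial.

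**Effect on the primary analysis**

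The sample size in {14} reproduces without any harms input: n = (1.960 + 1.282)² × 2 × 0.78 × 0.22 / 0.10² = 361 per group, 722 in total. Allowing for 20% loss gives 361/0.8 = 451.25, rounded up to 452 per group, or 904. Widening the side-effect window changes none of this.

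**The case against.** **The questionnaire is not shown.** Neither the questionnaire nor the list of specified reactions is in the article, and {12} refers to the registry for the full list of outcomes. Candidiasis may be recorded elsewhere. This stands as a limit: the article shows what its stated rule would exclude, not that later candidiasis goes unrecorded in practice. But the rule says that only reactions during treatment are collected, and nothing else in the article qualifies it.

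**Candidiasis may start during the course.** The Background wording can mean a consequence of antibiotics that begins while they are still being taken. Such cases would be counted if candidiasis is on the list. This also stands, and it is why no missed fraction can be claimed.

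**An on-treatment window has a rationale.** Under {11d} some women will use additional BV treatment, and {14} assumes that 22% will not have resolution at 4 weeks. A plain 28-day count would attribute reactions to the additional treatment to the first one. This is a fair objection to a simple extension of the window, and the fix has to deal with it.

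**A tempting stronger reading.** A reader might infer that side-effect proportions cannot be compared between arms because course lengths differ. The documents do not support that. The only documented difference is one day, no control regimen shorter than 6 days appears, and reactions per course is a legitimate measure of tolerability. The summary is also purely descriptive. A reader might likewise infer that three quarters of candidiasis is lost, but that rests on an even spread of onset for which the article gives no basis.

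**Limited importance.** The drugs are licensed and their safety is well known, serious events are not confined to the treatment period, and the stated value of the trial is less antibiotic use. These points keep the concern secondary. They do not explain why a questionnaire completed at week 4 should ignore the last three weeks for the listed reactions.

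**Conclusion.** The concern holds in a limited form. As written, a listed reaction that starts after the 6- or 7-day course is not counted, although the Background says that candidiasis often follows antibiotic treatment. The uncounted period is 22 of 28 days for dequalinium and 21 of 28 for 7-day metronidazole. The number of events lost cannot be stated.

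The consequence is a possible understatement of a harm difference in a descriptive secondary outcome. The primary non-inferiority analysis and the sample size are unaffected. The conclusion assumes that the article's sentence reflects the full protocol and the questionnaire, and that candidiasis is not captured by another item. It does not extend to calling the arms non-comparable because of course length.

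**What to change.** 1. On the week-4 questionnaire, ask about the specified reactions, including thrush, from first dose to the day of completion, each marked as during or after treatment.
2. Keep the during-treatment summary. Add a common 4-week summary by arm, grouped by treatment received as {20a} already requires.
3. Show the 4-week summary overall and with reactions after any additional BV treatment separated, using the data already collected under {11d}. The article mentions the treatment and the amount there but no date, so a before-or-after tick may be needed to place a reaction in time.
4. If candidiasis after treatment is already captured elsewhere, correct {22} to say so. No new item for candidiasis is then needed.

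The cost is a mid-trial amendment through the approvals listed in {25}. Only women followed up after the change would have the longer window. The Trial status section reports 452 recruited at manuscript submission, so 904 − 452 = 452 were still to join at that point. The two windows must be reported as separate outcomes. Nothing is lost from the existing summary, and no treatment changes.

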### Frequency and plans for auditing trial conduct {23}

An ongoing review of trial conduct will be undertaken by the trial management team as per the trial monitoring plan. Audits may be carried out by the sponsor or NCTU quality assurance teams in accordance with their local auditing plans.

### Plans for communicating important protocol amendments to relevant parties (e.g. trial participants, ethical committees) {25}

Any amendments made to the trial protocol will undergo review and approval by the sponsor, MHRA, Research Ethics Committee and Health Research Authority prior to implementation. Updated versions of the protocol will be shared with recruiting centres via email and uploaded to the trial website. Any substantial amendments made will also be communicated to the trial registry.

## Dissemination plans {31a}

The results of the trial will be published in the NIHR Journals Library and will be submitted for publication in a peer-reviewed journal. Participants who provided consent to receive the trial results will be emailed a research result summary following publication and this will also be made available on the trial website.

## Discussion

To our knowledge, this is the first randomised trial in patients with confirmed BV where they can screen and participate without the need to attend any in-person consultations with a healthcare provider.

Since the start of the COVID-19 pandemic, one of the challenges we faced was how to design the trial to ensure screening and recruitment could continue to take place despite national lockdowns which may prevent patients from accessing in-person clinical care. To address this, we implemented the two remote recruitment pathways. The introduction of a website recruitment pathway will improve the generalisability of the results for the trial as it opens up the trial to all women in the UK creating a much larger, more diverse group of potential participants, compared to those attending a local sexual health clinic. We hope that it will encourage women who may not feel comfortable visiting their GP or local sexual health clinic with their BV symptoms to participate as there is no in-person contact and all trial samples can be taken privately at home.

To support the identification and recruitment of patients, we have designed and launched an advertising campaign for the trial on social media and search engines. Our social media adverts are targeted to specific demographics using a range of different images of women who represent our target age groups and a diverse range of ethnicities. We will monitor the engagement of each of the adverts to see which are the most successful and whether this is impacting the demographic of the participants that we are recruiting.

A limitation to the trial design is the reliance of pathway 3 recruitment on the advertising campaign and overall success of publicising the trial. As women will not be introduced to the trial in the traditional format, during a consultation, it is important that we have full oversight and understanding of the advert engagement statistics and continue to develop campaigns in collaboration with our patient and public involvement reps to ensure the adverts remain relevant and appealing. Additionally, whilst we have implemented a number of different methods to keep participants engaged following recruitment, we are unsure whether the recruitment approach (in-clinic or remote) will impact the overall adherence to treatment and trial retention but we will monitor this closely.

The results from this trial will provide important information on the effectiveness of dequalinium chloride and usual care antibiotics on treating BV symptoms and provide us with valuable information on how to best manage BV patients and could potentially reduce the number of antibiotics prescribed to treat this condition.

## Trial status

At the time of the initial manuscript submission, 452 patients had been recruited. The first participant was recruited on 25 Aug 2021, and recruitment is planned to close on 31 December 2022 with a 3-month follow-up.

## Data Availability

Data sharing is not applicable to this article as no datasets were generated or analysed in preparation of this publication. De-identified participant data will be made available, upon request, in accordance with the NCTU standard operating procedures following the publication of the trial results.

## Abbreviations

BV: Bacterial vaginosis
CACE: Complier average causal effect
DMC: Data monitoring committee
EOI: Expression of interest
GUM: Genitourinary medicine
ICF: Informed consent form
NCTU: Nottingham Clinical Trials Unit
PIS: Patient information sheet
PPI: Patient and public involvement
RCT: Randomised control trial
SAE: Serious adverse event
SAP: Statistical analysis plan
STI: Sexually transmitted infection
SWAT: Study within a trial
TMG: Trial Management Group
TSC: Trial steering committee
